## Abstract

**Background:**

Globally, just 21% of the estimated 58 million people living with hepatitis C virus (HCV) know their status. Thus, there is considerable need to scale-up HCV testing if the World Health Organization (WHO) 2030 hepatitis elimination goals are to be achieved. HCV self-testing may assist with this; however, there are currently no data on the real-world impact of HCV self-testing.

With an estimated 5% of the general population living with HCV, Pakistan has the second highest HCV burden in the world. This study aims to evaluate the acceptability and impact of home delivery of HCV self-testing for secondary distribution in the context of a house-to-house HCV micro-elimination programme in Pakistan.

**Methods:**

This is a parallel group, non-blinded, cluster randomised trial comparing secondary distribution of HCV self-testing with secondary distribution of information pamphlets encouraging individuals to visit a testing facility for HCV screening. The cluster allocation ratio is 1:1. Clusters will be randomised either to HCV self-testing distributed via study staff or control clusters where information on HCV will be given and the participant will be requested to attend their local hospital for HCV screening. In both clusters, only households with a member who has not yet been screened as part of the larger micro-elimination project will be included. The primary outcome is the number and proportion of participants who report completion of testing. Secondary outcomes include the number and proportion of participants who a) receive a positive result and are made aware of their status, b) are referred to and complete HCV RNA confirmatory testing, and c) start treatment. Acceptability, feasibility, attitudes towards HCV testing, and cost will also be evaluated. The target sample size is 2,000 participants.

**Discussion:**

This study will provide the first ever evidence regarding secondary distribution of HCV self-testing. By comparing HCV self-testing with facility-based testing, we will assess whether HCV self-testing increases the uptake of HCV testing. The findings will inform micro-elimination programmes and determine whether HCV self-testing can enable individuals to be reached who may otherwise be missed.

**Trial Registration:**

This study and was registered on clinicaltrials.gov (NCT04971538) 21 July 2021.

**Supplementary Information:**

The online version contains supplementary material available at 10.1186/s12889-022-13125-9.

## Background

Hepatitis C virus (HCV) is a leading cause of liver cancer globally; however, just 21% of the 58 million individuals living with HCV have been diagnosed [1]. The diagnosis of HCV currently involves a two-step process: first, a person receives a facility-based serological test for HCV antibodies, then, if the result is positive, they receive a second test to assess for viraemia [2]. The World Health Organization (WHO) recommends treating all individuals with viraemia with directing-acting antiviral (DAA) therapy [2].

There is an urgent need to scale-up HCV testing to achieve the WHO 2030 hepatitis elimination goals [3]. In July 2021, WHO announced the first ever recommendations for HCV self-testing, which state that HCV self-testing should be offered as an additional approach to serological testing for HCV antibodies [4]. Self-testing refers to a process where an individual, either alone or with someone they trust, performs a test and interprets the result [4].

HCV self-testing has been shown to be a feasible and acceptable testing approach that individuals perceive to be a tool that offers a convenient and private way for them to learn of their hepatitis C status [5–10]. However, there are currently no data on the real-world impact of HCV self-testing, including its effect on uptake of testing and linkage to care.

With an estimated 5% of its general population living with HCV, Pakistan has the second highest burden of this infection in the world [11]. A major scale-up of testing and treatment is needed if Pakistan is to eliminate HCV [12]. The current micro-elimination programme, led by Aga Khan University (AKU), is taking place in three Union Councils (UC) of Malir District in Karachi, Pakistan: UC-9 (Darsano Chano), UC-10 (Malh) and UC-11 (Murad Memon). This micro-elimination programme brings HCV screening, diagnostic and treatment services to people’s doorsteps and aimed to test around 30,000 people, as described previously [13]. However, the current programme has not been able to screen the entirety of the planned coverage area due to an estimated 39% of household members being absent when AKU staff made their field visits. The present study will assess whether secondary distribution of HCV self-testing can increase testing uptake among individuals who were unavailable during the visit by testing campaign staff. In the context of HIV, the secondary distribution of HIV self-tests during door-to-door testing campaigns substantially increased testing coverage (by 21%) among absent individuals or those who declined to participate [14]. The current study will be the first to explore this mode of delivery of self-testing for HCV.

### Study aim and objectives

This study aims to evaluate the acceptability and impact of the secondary distribution of HCV self-tests in the context of a house-to-house HCV micro-elimination programme in Malir district, Karachi division, Pakistan. The primary objective is to assess the impact of HCV self-testing on HCV antibody testing rates. The secondary objectives are to assess the impact of HCV self-testing on linkage to and completion of HCV RNA confirmatory testing in HCV antibody-positive individuals and treatment initiation in HCV RNA-positive individuals eligible to begin treatment; to assess the acceptability and feasibility of HCV self-testing; and to assess the cost and cost-effectiveness of HCV self-testing compared with facility-based testing.

## Methods/design

### Design

This is a parallel group, non-blinded, cluster randomised superiority trial comparing the secondary distribution of HCV self-tests with the secondary distribution of information pamphlets encouraging individuals to visit a testing facility for HCV screening. A subset of participants (*n* = 120) from both the intervention and control groups will be asked to participate in face-to-face interviews regarding their perceptions of the testing experience, to provide insights into the acceptability and feasibility of HCV self-testing. The study timeline is shown in Table 1.

**Table 1 Tab1:** Study timeline

	**Enrolment**	**Follow-up for all participants**	**Follow-up for HCV antibody-positive participants**
**Procedure**	**Day 1**	**Months 1–2**	**Months 1–8**
Inclusion and exclusion criteria	X		
Informed consent obtained	X		
HCV antibody testing (either HCV self-test left with the household or participants in the control group attend Memon Goth Hospital)	X	X	
Collection of test results and survey of perceptions of the testing process		X	
Referral of HCV antibody-positive individuals for confirmatory testing and linkage to care		X	X
Linking of data for the RDT (control group) and RNA test and treatment initiation (as applicable for the intervention and control groups)		X	X
Adverse event (AE)/serious adverse event (SAE) review	X	X	X
Cost data collection and analysis	X	X	X

### Study setting

The study will take place in the Malir district of Karachi, Pakistan. Darsano Chano (UC9) is in a rural area and has a population of approximately 10,000 individuals. Malh (UC10) is peri-urban and has a total population of approximately 50,000 individuals. Both UCs have small, well-established community clinics, which have formed the hub of the larger ongoing HCV micro-elimination programme. UC9 and UC10 have approximately 2,000 and 10,000 households, respectively, with an average of five family members per household.

The study will take place at the homes of eligible adults visited by study staff. Based on the current micro-elimination programme, an estimated 7,500 participants remain in both UC9 and UC10 who have not yet been tested as part of the larger micro-elimination programme. Each UC has been subdivided into ten blocks/clusters, based on neighbourhood geography, as shown in Figs. 1 and 2; these clusters have not yet been randomised, but will be matched-pair randomised on a 1:1 basis.

**Fig. 1 Fig1:**
[figure not shown]
Map of UC9. Maps created using Adobe Illustrator 25.4 for Windows. https://www.adobe.com/ro/products/illustrator.html?skwcid=AL!3085!3!341240180390!e!!g!!adobe%20illustrator&mv=search&sdid=KCJMVLF6&ef_id=CjwKCAiAgbiQBhAHEiwAuQ6Bknh2k612ZgbuSDwblwUKE5L1T1KaZATGaxTwAGIkknQrdcWhGZ6JrxoCtNAQAvD_BwE:G:s&s_kwcid=AL!3085!3!341240180390!e!!g!!adobe%20illustrator!1478481991!58339249918&gclid=CjwKCAiAgbiQBhAHEiwAuQ6Bknh2k612ZgbuSDwblwUKE5L1T1KaZATGaxTwAGIkknQrdcWhGZ6JrxoCtNAQAvD_BwE

**Fig. 2 Fig2:**
[figure not shown]
Map of UC10. Maps created using Adobe Illustrator 25.4 for Windows. https://www.adobe.com/ro/products/illustrator.html?skwcid=AL!3085!3!341240180390!e!!g!!adobe%20illustrator&mv=search&sdid=KCJMVLF6&ef_id=CjwKCAiAgbiQBhAHEiwAuQ6Bknh2k612ZgbuSDwblwUKE5L1T1KaZATGaxTwAGIkknQrdcWhGZ6JrxoCtNAQAvD_BwE:G:s&s_kwcid=AL!3085!3!341240180390!e!!g!!adobe%20illustrator!1478481991!58339249918&gclid=CjwKCAiAgbiQBhAHEiwAuQ6Bknh2k612ZgbuSDwblwUKE5L1T1KaZATGaxTwAGIkknQrdcWhGZ6JrxoCtNAQAvD_BwE

Participants in the control clusters will be directed to Memon Goth Hospital for facility-based HCV testing; if a participant tests positive by HCV rapid diagnostic test (RDT), they will immediately have blood drawn for viraemia testing. As described below, for those in the self-test group who report a positive self-test, a member of the AKU team will come to their house to perform a blood draw for viraemia testing and liver staging. Treatment for both groups will be provided at each participant’s doorstep, free of charge, through a partnership between AKU and The Liver Foundation.

As there is currently no quality-assured HCV self-test available, the professional-use OraQuick® HCV Rapid Antibody Test, which has been adapted by the manufacturer for self-testing by being repackaged and labelled with instructions for use, will be used in this trial. The OraQuick® HCV Rapid Antibody Test is prequalified by WHO and CE-marked for professional use (sensitivity 98.1%, specificity 99.6%). The OraQuick® HCV Self-Test kits provided to participants in the intervention group will be labelled for Research Use Only (RUO).

### Eligibility criteria

Participants are only eligible to be included in the trial if they meet all of the following inclusion criteria: ≥ 18 years of ageResiding in UC9 or 10Not yet reached for testing as part of the larger micro-elimination programmeNot known to be HCV antibody-positiveNot tested for HCV within the past 6 monthsEligible for inclusion in the larger micro-elimination programme

Participants will be excluded from the trial if they are at home on the day that AKU study staff visit to either leave an HCV self-test or the information materials encouraging those who were previously missed to attend for facility-based HCV testing.

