### Trial processes and intervention

The neighbourhoods in UCs 9 and 10 will be grouped into clusters. These clusters will be matched in terms of similarity of geography (peri-urban or rural), population size, and age demographics. Each member of a matched cluster pair will be randomised to the intervention or control groups.

As outlined in Fig. 3, AKU study staff will return to the households where individuals were missed during the first round of house-to-house screening carried out as part of the larger micro-elimination programme. In the intervention group, the study staff will leave as many HCV self-tests as there were individuals missed from the first round of house-to-house screening who are still not present during the visit, as well as instructions for use, with the most senior member of the household present. The study team will also explain the HCV self-testing process, using a standardised explanatory checklist, to that same senior member of the household; they will also leave a mobile phone number for the participant to call if they need help in conducting the test. Participants will be provided with various types of support to minimise the occurrence of errors during the self-testing process and any possible confusion in interpretation of the test results. Printed instructions for use in Urdu will be delivered with the test kits, which will also contain pictorial guides on how to use the test. Participants will have access to a live chat facility and a call centre.

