**Fig. 3 Fig3:**
[figure not shown]
Trial flow diagram

In the control group, if the participant(s) are not at home, the study staff will leave information about HCV testing and direct them to the nearest clinic that offers HCV testing services; the participant(s) will not be left an HCV self-test. Study staff will however leave a mobile phone number for the participant(s) to call if they need further information on HCV testing.

In both groups, if no-one is at home or no one aged 18 years or more is present, the study staff will make as many return visits as necessary to contact a household member.

A small incentive, comprising a 500 rupee (approximately 3 USD) phone credit voucher, will be provided to participants in both the intervention and control groups for any information they return via a phone call, including whether they took the test and, if so, what the result was. During this return phone call, the study team will follow up with the participant to inquire whether they completed the test, record any test results, and conduct a brief interview.

For all participants who report a positive HCV antibody test, study staff will make an appointment to return to their house to enrol them in the larger micro-elimination programme. During this home visit, they will complete a blood draw for HCV viraemia testing and APRI (aspartate aminotransferase to platelet ratio index) liver staging, to be performed at Memon Goth Hospital. The viraemia testing will be performed using an HCV core antigen assay (ARCHITECT HCV Ag assay, Abbott® Diagnostics). If a participant’s result is in the grey zone (≥ 3 to ≤ 10 fmol), a second sample from the same participant will be tested for HCV RNA (Xpert HCV Viral Load, GeneXpert® IV, Cepheid, France) to determine viraemia. If the participant is viraemic, further care and treatment will be provided to their doorstep. All participants who report a negative HCV antibody test will be encouraged to seek a retest, as per the national guidance.

Approximately 1 month following the start of enrolment, face-to-face interviews will be conducted with a subset of participants in both the intervention and control groups, to explore their perceptions of the testing process.

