As this study is intended to measure whether there is an increase in testing following the secondary distribution of HCV self-testing compared with the standard of care facility-based testing, facility-based testing was chosen as the comparator. In both groups, if a previously missed individual is at home when a study staff member visits, they will enrol the person in the larger micro-elimination programme (and not this study).

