#### Assignment of interventions: allocation

Each member (neighbourhood block) of a matched cluster pair will be randomly allocated to the intervention or control group using a simple, computer-generated randomisation list. Each matched pair will be established based on similarities in type of geography (urban/peri-urban or rural), population size, sex distribution, age range, income and literacy. Within each UC and type of cluster (rural versus peri-urban), clusters will be put into pairs based on average household size (i.e. total estimated population in the cluster divided by the number of structures in the cluster). For example, the two rural clusters with the two largest average household sizes will be paired, followed by the next two rural clusters with the third and fourth largest average household sizes, and so on. Similar pairing will be performed for peri-urban clusters. If there are more than two clusters with the same average household size, then the estimated average age will be used as a tiebreaker, and pairs will be selected based on the closest estimated average age in those clusters. Once all clusters have been put into pairs, each member of a pair will be randomised to the intervention or control group.

For the face-to-face interviews, a subset of the main participants will be selected. Based on the study cluster assignment and testing results, study participants will be divided into the following eight subgroups:

Intervention group:In a rural cluster in the intervention group and completed a testIn a rural cluster in the intervention group, but did not complete a testIn a peri-urban cluster in the intervention group and completed a testIn a peri-urban cluster in the intervention group, but did not complete a test

Control group:In a rural cluster in the control group and completed a testIn a rural cluster in the control group, but did not complete a testIn a peri-urban cluster in the control group and completed a testIn a peri-urban cluster in the control group, but did not complete a test

For each subgroup, a randomly ordered list of participants will be generated via computerised randomisation. Then, for each subgroup, participants will be contacted by study staff in descending order on the list until a maximum of 15 individuals in each subgroup have completed the survey.

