The trial is not blinded, and the participants and study staff know which group the participants are assigned to; therefore, no additional concealment mechanisms will be used.

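### Trial membership is settled after randomisation by staff who know the arm, and concealment is waived only because the trial is open

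*Protocol article*

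**What the plan says.** All references are to the protocol article.

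- **Order of events.** Under Assignment of interventions: allocation: "Once all clusters have been put into pairs, each member of a pair will be randomised to the intervention or control group". Whole neighbourhood blocks are allocated, and the household visits that deliver kits or pamphlets come afterwards.
- **Who is excluded.** Under Eligibility criteria: "Participants will be excluded from the trial if they are at home on the day that AKU study staff visit". Trial processes and intervention says where such people go: "if a previously missed individual is at home when a study staff member visits, they will enrol the person in the larger micro-elimination programme". This applies in both groups.
- **Who enters.** In the intervention arm, the number of kits left equals the number of "individuals missed from the first round of house-to-house screening who are still not present during the visit". In the control arm, staff leave information for those not at home.
- **Knowledge of the arm.** The allocation section closes by saying that "the participants and study staff know which group the participants are assigned to; therefore, no additional concealment mechanisms will be used".
- **What the count feeds.** Table 3 and the formulas below it divide completed tests by all participants in the arm: (a+b+c+d+e) for intervention and (f+g+h+i+j) for control.

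The Limitations section covers contamination, attrition and detection bias. It does not mention selection of participants after randomisation.

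**The concern.** Randomising clusters balances the people living in them. It does not by itself balance a subgroup picked out within clusters later, by people who know the allocation. Here the subgroup is those still absent at a visit that carries arm-specific material. If visits in one arm fall more often at hours when employed or younger adults are out, or if absence and prior testing are noted more carefully in one arm, the two sets of participants can differ before any test is offered. The primary comparison then mixes that difference with the effect of self-testing.

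The reason given for using no concealment makes this worse. Blinding concerns who knows the arm during treatment and outcome assessment. Concealment concerns whether the people to be counted are fixed before the arm is known. The first is impractical here and the second is not.

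**Working it through.** The plan states no figure on this point, so the main check is the sequence of steps. The arithmetic is illustration only.

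**1. Sequence.**

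| Step | Place in the article | Before or after allocation |
|---|---|---|
| People missed in round one are known to the programme | Study setting (an estimated 7,500 not yet tested); Trial processes and intervention | Before |
| Clusters paired and randomised | Assignment of interventions: allocation | Allocation |
| Visit: at home means out, absent means in | Eligibility criteria; Trial processes and intervention | After, by staff who know the arm |
| Other criteria checked (no recent test, not known antibody-positive) | Table 1, Day 1 | After; the person concerned is absent by definition |

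The candidate pool is therefore fixed before allocation, and the final selection from it is made after.

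**2. The inference about concealment.** The premise is that staff and participants know the group. The conclusion is that no concealment is used. The premise rules out blinding. It does not prevent listing the candidates in each cluster before the allocation is released, so the conclusion does not follow.

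**3. What remains open after allocation.** Two things: when each household is visited, and how absence and the other criteria are recorded. The article describes a physical count in the intervention arm (one kit per absent person) and no matching per-person count in the control arm. Both go into the Table 3 denominators.

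**4. Illustrative size.** The article gives no completion rates, so every rate below is assumed.

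*Different mix.* Suppose easier-to-reach people complete testing at 60% and harder-to-reach people at 40%, under the same offer.
- Easier group 60% of the sample: 0.6×60 + 0.4×40 = 52%.
- Easier group 50%: 0.5×60 + 0.5×40 = 50%.
- Easier group 40%: 0.4×60 + 0.6×40 = 48%.

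The spurious difference between arms is 52 − 50 = 2 points or 52 − 48 = 4 points.

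*Omission in one arm.* Let the true rate be p, and let a fraction f with completion rate r not be entered in that arm. The observed rate is (p − f·r)/(1 − f).
- p = 60%, f = 10%, r = 0: 0.60/0.90 = 66.7%, a shift of 6.7 points.
- p = 60%, f = 10%, r = 30%: (0.60 − 0.03)/0.90 = 63.3%, a shift of 3.3 points.
- p = 60%, f = 5%, r = 0: 0.60/0.95 = 63.2%, a shift of 3.2 points.
- p = 60%, f = 5%, r = 30%: (0.60 − 0.015)/0.95 = 61.6%, a shift of 1.6 points.

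The Statistical methods section judges the lower 97.5% confidence limit against 20 points, so shifts of this order could matter for a result near the margin.

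**The case against.** The strongest reply is that staff have little to decide. Candidates come only from the round-one missed group. Being at home is a matter of fact, and the rule is worded identically for both arms. Excluding people found at home also defines the intended population. Pairing follows a stated rule and whole clusters are allocated by a computer-generated list, so there is no individual sequence for staff to predict. All of this stands, and it limits the risk. It does not remove it, because identical wording does not ensure identical application by staff who know the arm.

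Three stronger readings are tempting, and the documents do not support them.

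- **Staff may revisit a household until the person they want is absent or present.** The article does say staff will "make as many return visits as necessary to contact a household member", but only where nobody, or no adult, is at home to receive the materials, and in both groups.
- **Recent testing and known status are applied later, among callers only.** Nothing in the article applies eligibility at the results call, which is described as covering consent, results and a short interview. Table 1 puts eligibility on Day 1, when an adult household member is present and can be asked, however imperfectly.
- **The bias is 2 to 4 points.** Those figures come from assumed rates. The 4-point value needs a 20-point difference between arms in the mix of people, which nothing in the article suggests.

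The full protocol may set visit hours or a listing procedure. That would answer part of the point, but the sentence on concealment would still be wrong as written.

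**Conclusion.** The point holds in limited form. Membership of the trial is settled after allocation by staff who know the arm, and the reason given for using no concealment is not a valid one. The documents show that the arms can differ in who is counted. They do not show that they do, nor in which direction. The size cannot be derived from the article. The shifts worked through above (1.6 to 6.7 points) rest wholly on assumed completion rates and assumed imbalances. The change is worth making because the affected quantity is the primary denominator and the remedy is cheap. It is not a reason to regard the design as unsound.

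**What to change.** 1. Freeze a dated roster of round-one missed adults for each cluster, from existing programme records, before staff learn the allocation. Use it as the only candidate list in both arms.
2. Visit both clusters of a pair over the same mix of weekdays and hours. The roster alone is not enough, because at-home exclusions still occur after allocation.
3. Record the remaining criteria (recent test, known status) at the Day 1 visit from the household informant, on the same form in both arms. Programme records may not hold this for people the programme never reached.
4. Report by arm and cluster the numbers rostered, found at home, otherwise excluded and entered, so that the counts add up to the roster. Add a sensitivity analysis on the full roster. Its contrast will differ from the primary one, because people found at home are taken into the larger programme in either arm.
5. Replace the sentence on concealment with a statement of when the roster was fixed relative to allocation, and add post-randomisation selection to Limitations.

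Trial status says enrolment began in November 2021. For visits already made, items 1 to 3 come too late, and the dated round-one list should be used for item 4.

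The cost is a visit schedule organised by pair and a little more analysis. The roster should come from records the programme already needs in order to return to these households.
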